### Intervention

This study aims to assess the impact of IMT on enhancing oxygenation levels during painless gastroscopy in individuals with a BMI of 35–39.9 kg·m^−2^. Upon identifying the participants, an intervention delivery schedule will be established. Before undergoing gastroscopy, participants will follow a 4-week IMT intervention protocol based on their assigned group. The timeline for enrollment, interventions, and assessments is outlined in detail in Table 1. All data will be collected according to the participant’s specific timeline, which includes the following time points: T1: 1 day before IMT, T2: immediately prior to anesthesia, T3: at the conclusion of the gastroscopy, T4: on the night of the gastroscopy, T5: 1 week after the gastroscopy, and T6: 4 weeks after the gastroscopy.

For participants assigned to the intervention group, a research assistant will measure their Pi(max) using the IMT device (POWER^®^breathe, Tianrui, Jiangsu). During the measurement process, patients will be seated and wear a nasal clip. They will exhale slowly and completely, followed by inhaling with maximum force and holding it for at least 1.5 s. The inspiratory pressure at this point will be recorded. This process will be repeated three times, and the average of the recorded inspiratory pressures will be considered as the Pi(max).

POWER^®^breathe follows a standard practice of conducting 30 inspiratory breaths twice a day (20). The intervention group will undergo IMT using a load equivalent to 30% of their Pi(max) during the first week. Starting the following week, the load will be increased by 10% each week for a total of three adjustments. On the other hand, participants in the control group will not receive any load during the 4-week IMT. It is important to note that participants will not be informed about their assignment to either the intervention or control group.

### Monitoring and standard practice-based anesthesia protocol

To enhance subject compliance with IMT, all participants will receive comprehensive information about the procedure and specifics of IMT. Additionally, they will be remotely instructed in real-time by an independent research assistant using video software. In this study, adjusted body weight will be utilized, calculated as follows: ideal body weight + 0.4 × (total body weight-ideal body weight) (9). In order to mitigate the risk of potential complications during sedation, we will ensure the presence of standby equipment, including HFNC, anesthesia machines, laryngeal masks, endotracheal catheters, and laryngoscopes.

Upon arrival at the endoscopy center, all subjects will be positioned in the left decubitus position and undergo routine monitoring, which includes non-invasive blood pressure, electrocardiography, heart rate (HR), peripheral oxygen saturation (SpO_2_), respiratory rate, and end-tidal carbon dioxide levels.

The procedure will be conducted in the following steps:

Firstly, before administering procedural sedation, patients will receive oxygen through a nasal tube at a flow rate of 3 L∙min^−1^ and will be instructed to take 10 deep breaths.

Secondly, intravenous administration of esketamine at a dose of 0.5 mg·kg^−1^ will be carried out within 10 s. Simultaneously, remimazolam tosilate will be infused using a micromedicine infusion pump at a rate of 12 mg·kg^−1^·h^−1^ until the Modified Observer’s Assessment of Alertness and Sedation (MOAA/S) score reaches 1, as indicated in Table 2.

**Table 2 tab2:** Modified observer’s assessment of alertness/sedation scale.

Score	Responsiveness
5	Responds readily to name spoken in normal tone
4	Lethargic response to name spoken in normal tone
3	Responds only after name is called loudly and/ or repeatedly
2	Responds only after mild prodding or shaking
1	Responds only after painful trapezius squeeze
0	Does not respond to painful trapezius squeeze

Thirdly, to prevent the tongue from falling back, a suitable nasopharyngeal airway with end-tidal carbon dioxide monitoring will be carefully inserted into the patient’s nasal cavity. At this stage, gastroscopy will be performed by an experienced endoscopist.

Throughout the procedure, remimazolam tosilate dosage will be dynamically adjusted based on the reference bispectral index (BIS), which is determined when the MOAA/S score reaches 1, to maintain a stable level of sedation.

If any involuntary movements, such as coughing, raising the head, or body shifting, are observed in a patient, an immediate infusion of remimazolam tosilate at a dose of 0.05 mg·kg^−1^ will be administered. If such movements persist after 1 min, a reapplication of remimazolam tosilate may be necessary. After the examination, all patients will be transferred to the PACU for recovery.

In cases where the heart rate is less than 45 beats per minute or exceeds 100 beats per minute, Atropine at a dose of 0.5 mg or Esmolol at a dose of 1 mg·kg^−1^ will be administered separately to address the situation. Similarly, if the mean arterial pressure deviates by more than 20% from the baseline, Phenylephrine at a dose of 40 μg or Urapidil hydrochloride at a dose of 12 mg will be promptly administered accordingly.

If a patient’s SpO_2_ falls below 90%, the experienced anesthesiologist must differentiate between respiratory obstruction and respiratory depression (34). For respiratory obstruction, the anesthesiologist will apply jaw-lift. On the other hand, respiratory depression will be managed using appropriate measures such as positive-pressure ventilation using a bag-mask.

If deemed necessary, flumazenil will be employed to counteract the effects of remimazolam tosilate. However, in the event of severe hypoxemia and if the aforementioned methods prove ineffective, the anesthesiologist will promptly administer either a laryngeal mask or perform endotracheal intubation to ensure adequate airway management.

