**Outcome assessment**										
(1) The incidence of hypoxemia					X					
(2) The need for airway maneuvers					X					
(3) Blood pressure		X		X	X		X			
(4) Sleep quality		X		X				X	X	X
(5) Pro-inflammatory cytokines levels		X		X		X				
(6) Adverse events					X		X			
**Requirement for vasoactive agents**					X		X			
**Need for rescue sedatives**					X		X			

IMT, inspiratory muscle training; PACU, post-anesthesia care unit; Pi(max), maximum inspiratory pressure; MOAA/S, Modified Observer’s Assessment of Alertness and Sedation; BIS, bispectral index; T1, 1 day before IMT; T2, immediately prior to anesthesia; T3, at the conclusion of the gastroscopy; T4, on the night of the gastroscopy; T5, 1 week after the gastroscopy; T6, 4 weeks after the gastroscopy.

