### Primary outcomes

The primary outcome of this study is the incidence of hypoxemia during painless gastroscopy. Hypoxemia will be defined as a SpO_2_ level below 90%.

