### Secondary outcomes

The secondary outcomes encompass several measures, including the need for airway maneuvers, blood pressure changes, sleep quality assessment, pro-inflammatory cytokine levels, and monitoring of adverse events such as bradycardia, tachycardia, nausea, and vomiting.

For this study, airway maneuvers will be defined as jaw-lift, positive-pressure ventilation with a bag-mask, insertion of a laryngeal mask, or endotracheal intubation.

Blood pressure will be measured at different time points: before IMT, prior to anesthesia, during the examination, and in the PACU.

Sleep quality and duration will be assessed using the Pittsburgh Sleep Quality Index (PSQI), a 19-item questionnaire (Table 3), at T1, T2, T4, T5, and T6. A patient scoring greater than 5 on the PSQI will be classified as a poor sleeper (35).

**Table 3 tab3:** The questionnaire of Pittsburgh Sleep Quality Index.

1. During the past month, when have you usually gone to bed?				
2. During the past month, how long (in minutes) has it taken you to fall asleep each night?	≤15 min (0)	16 ~ 30 min (1)	31 ~ 60 min (2)	>60 min (3)
3. During the past month, when have you usually gotten up in the morning?				
4. During the past month, how many hours of actual sleep did you get that night? (This may be different than the number of hours you spend in bed)	>7 h (0)	6 ~ 7 h (1)	5 ~ 6 h (2)	<5 h (3)
5. During the past month, how often have you had trouble sleeping because you…	Not during the past month (0)	Less than once a week (1)	Once or twice a week (2)	Three or more times a week (3)
a. Cannot get to sleep within 30 min	(0)	(1)	(2)	(3)
b. Wake up in the middle of the night or early morning	(0)	(1)	(2)	(3)
c. Have to get up to use the bathroom	(0)	(1)	(2)	(3)
d. Cannot breathe comfortably	(0)	(1)	(2)	(3)
e. Cough or snore loudly	(0)	(1)	(2)	(3)
f. Feel too cold	(0)	(1)	(2)	(3)
g. Feel too hot	(0)	(1)	(2)	(3)
h. Have bad dreams	(0)	(1)	(2)	(3)
i. Have pain	(0)	(1)	(2)	(3)
j. Other reason(s), please describe, including how often you have had trouble sleeping because of this reason(s)	(0)	(1)	(2)	(3)
6. During the past month, how often have you taken medicine (prescribed or “over the counter”) to help you sleep?	Not during the past month (0)	Less than once a week (1)	Once or twice a week (2)	Three or more times a week (3)

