Fourth, our study’s findings may hold promising implications for clinical application. Existing evidence has highlighted the potential of short-term loaded IMT to enhance respiratory muscle function, subsequently improving oxygenation levels (24–26). Should this intervention effectively mitigate the occurrence of hypoxemia among obese patients during painless gastroscopy, it will result in decreased reliance on airway interventions and fewer sedation-related complications. Consequently, this may streamline procedural sedation, delivering notable advantages to busy ambulatory endoscopy centers. Furthermore, these favorable outcomes will promote the progress and adoption of comfort-focused medical practices, especially within these distinct high-risk populations.

Last, we will explore its impact on blood pressure, sleep quality, and pro-inflammatory cytokines in obese individuals undergoing painless gastroscopy. Both procedural sedation and obesity can have negative effects on sleep and the cardiopulmonary system (17, 40), and pro-inflammatory cytokines play a role in sleep regulation and are associated with various diseases (41). Several studies have indicated that IMT can be used as an auxiliary means to reduce the tendency of upper airway collapse during sleep and improve sleep quality (17).

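### SpO2 below 90% defines the primary event and is the only stated trigger for the counted airway maneuvers, so an any-maneuver rate is not independent support for the primary

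*Protocol article*

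**What the plan says.** Four places in the protocol article bear on this point.

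- **Primary outcomes.** "Hypoxemia will be defined as a SpO_2_ level below 90" percent. No minimum duration is given.
- **Monitoring and standard practice-based anesthesia protocol.** When SpO2 "falls below 90%, the experienced anesthesiologist must differentiate between respiratory obstruction and respiratory depression". Then "For respiratory obstruction, the anesthesiologist will apply jaw-lift", while "respiratory depression will be managed using appropriate measures such as positive-pressure ventilation using a bag-mask". A laryngeal mask or intubation comes "in the event of severe hypoxemia and if the aforementioned methods prove ineffective". Flumazenil is available if judged necessary.
- **Secondary outcomes.** For this trial "airway maneuvers will be defined as jaw-lift, positive-pressure ventilation with a bag-mask, insertion of a laryngeal mask, or endotracheal intubation". No count, grade, timing or trigger is added. The nasopharyngeal airway that every patient receives is not on the list.
- **Table 1.** The row "2) The need for airway maneuvers" is marked in the same single column, the anesthesia and examination period, as the row for hypoxemia.

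Two further places matter for interpretation. Under Strengths of the study, the article expects that if training reduces hypoxemia, "it will result in decreased reliance on airway interventions and fewer sedation-related complications". The section on inclusion and exclusion criteria, read with Shedding criteria, takes out of the study any patient whose severe hypoxemia requires intubation.

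**The concern.** No counted maneuver has a stated trigger other than the reading that defines the primary event. If the secondary outcome is summarised as any maneuver versus none, a difference between arms in hypoxemia carries over into a difference in maneuvers through the treatment rule itself. A reader who sees both results favour training could take the second as corroboration, although it adds little.

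The link also works in the other direction. The rule says what happens once SpO2 is below 90%. It does not forbid acting earlier, and respiratory rate and end-tidal carbon dioxide are monitored throughout. A jaw-lift at, say, 91% may stop a primary event from occurring. Nothing in the outcome definition separates that maneuver from one made in response to hypoxemia, so the data could not show whether early action hides primary events, or hides more of them in one arm.

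Finally, the information that could set this outcome apart from the primary lies in which maneuver was used. One of the four types, intubation for severe hypoxemia, is also a ground for leaving the study.

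**Working it through.** **The plan's own figure first.** Inputs from Sample size: 40% versus 20%, power 90%, type I error 0.05 (taken as two-sided), 1:1 allocation. The unpooled normal approximation with rounded normal quantiles gives

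n per arm = (1.96 + 1.28)² × (0.40×0.60 + 0.20×0.80) / 0.20² = 10.4976 × 0.40 / 0.04 = 104.98, so 105.

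Enrolment: 105 × 1.10 = 115.5, so 116 per arm and 232 in total. The stated figures are reproduced, and nothing below disputes them.

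**Overlap if the rule is followed exactly.** Let p be the hypoxemia rate, a the probability of a counted maneuver given hypoxemia, and b the probability given no hypoxemia. The any-maneuver rate is m = a·p + b·(1 − p), and its correlation with the primary within an arm is

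phi = p·(a − m) / √[p(1 − p)·m(1 − m)].

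With a = 1 and b = 0, m = p and phi = 1 in both arms. In 105 evaluable patients per arm that is 0.40 × 105 = 42 and 0.20 × 105 = 21 patients, the same people for both outcomes (46.4 and 23.2 if all 116 per arm are counted).

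**Overlap if practice departs from the rule.** The documents give no values for a or b, so these are assumptions covering a range. Power uses the pooled two-proportion formula at 105 per arm, two-sided 0.05.

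| a | b | Any-maneuver rate, control vs intervention | phi, control / intervention | Power |
|---|---|---|---|---|
| 1.00 | 0 | 40% vs 20% | 1.00 / 1.00 | 0.891 |
| 0.95 | 0.05 | 41% vs 23% | 0.90 / 0.86 | 0.803 |
| 0.90 | 0.10 | 42% vs 26% | 0.79 / 0.73 | 0.690 |
| 0.80 | 0.20 | 44% vs 32% | 0.59 / 0.51 | 0.433 |

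Example, second row, control: m = 0.95×0.40 + 0.05×0.60 = 0.41; phi = 0.40×(0.95 − 0.41) / √(0.24×0.41×0.59) = 0.216 / 0.241 = 0.90.

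The overlap stays strong unless departures are large. In all these rows a and b are the same in both arms, so the whole difference in maneuver rates comes from the difference in hypoxemia.

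**Unmarked early maneuvers.** Patients without a primary event number 105 − 42 = 63 in the control arm and 105 − 21 = 84 in the intervention arm. If a share b of them had a maneuver started at SpO2 of 90% or above, then b = 0.05 means about 3 and 4 patients (3.15 and 4.2), and b = 0.20 about 13 and 17 (12.6 and 16.8). An outcome that counts SpO2 below 90% or such a maneuver has rate p + b(1 − p): 43% vs 24% at b = 0.05, 46% vs 28% at 0.10, and 52% vs 36% at 0.20. Power is 0.836, 0.775 and 0.648 respectively. This suits a sensitivity analysis, not a replacement for the primary. If b differs between arms, the primary comparison could shift in either direction; the documents do not say which.

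**The case against.** A fair defence has several parts, and most of it stands.

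- *The article never says the outcome is scored any versus none.* Correct. Secondary outcomes lists which actions count, and scoring may be fixed in a fuller document. The point therefore concerns an any-versus-none summary, if one is used, and not a plan that is stated.
- *The rule says what to do if SpO2 is below 90%, not only then.* Correct. In addition, bag-mask ventilation is given as an example, flumazenil is not a counted maneuver, and a brief dip could resolve while the cause is being sorted out. A reader might infer that the two outcomes are one event counted twice, or that the secondary adds no information. The text does not support that: the overlap is heavy but not an identity.
- *Jaw-lift and bag-mask ventilation are not rungs of one ladder.* Correct. The protocol assigns them to different causes, obstruction and depression; only laryngeal mask or intubation is an escalation. A reader might treat a move from bag-mask to jaw-lift as a milder course, but it could equally be a change of mechanism. An ordinal scale ranking the two has no basis in the document.
- *No one proposes to use this result as confirmation.* Largely correct. Strengths of the study presents fewer airway interventions as a consequence of less hypoxemia, and the Introduction only lists the outcome among the secondary ones. The risk lies in how the result is read, not in a stated claim.
- *Correlated secondary outcomes are ordinary.* True, and reporting how many patients needed help is legitimate.

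What the defence does not remove is the shared trigger, the missing mark on early maneuvers, and the possible loss of intubated patients.

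**Conclusion.** The concern holds in a limited form. SpO2 below 90% is both the primary event and the only stated trigger for the actions counted as airway maneuvers, so an any-maneuver rate would largely follow the primary and should not be offered as independent support. The correlation is 1.00 under strict adherence and between 0.90 and 0.51 under assumed departures of 5% to 20%; those departures are not taken from the protocol. Separately, maneuvers started at 90% or above are not forbidden and would not be identified, so the trial could not show whether they conceal primary events. How often this happens cannot be estimated from the document.

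This affects the reading of one secondary outcome and the robustness check on the primary. It does not affect the primary definition, the sample size or the primary test. It is a worthwhile, inexpensive improvement and not an error that undermines the trial.

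**What to change.** Leave clinical management as written and change only what is recorded and reported.

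1. Report maneuvers by type, per patient and by arm: jaw-lift, bag-mask ventilation, laryngeal mask, intubation. Do not rank jaw-lift against bag-mask. Keep patients intubated for severe hypoxemia in this analysis and in the primary analysis, and say so explicitly, because the shedding criteria could otherwise remove them.
2. Record SpO2 at the start of each maneuver. Add a sensitivity analysis of the primary in which an event is either SpO2 below 90% or a maneuver started at SpO2 of 90% or above.
3. State that the any-maneuver rate shares its trigger with the primary outcome and is to be read in that light.

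The cost is one or two extra fields on the procedure form and one extra sensitivity analysis. No staff, procedures or patient burden are added.

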### Primary outcomes

The primary outcome of this study is the incidence of hypoxemia during painless gastroscopy. Hypoxemia will be defined as a SpO_2_ level below 90%.

### Secondary outcomes

The secondary outcomes encompass several measures, including the need for airway maneuvers, blood pressure changes, sleep quality assessment, pro-inflammatory cytokine levels, and monitoring of adverse events such as bradycardia, tachycardia, nausea, and vomiting.

For this study, airway maneuvers will be defined as jaw-lift, positive-pressure ventilation with a bag-mask, insertion of a laryngeal mask, or endotracheal intubation.

Blood pressure will be measured at different time points: before IMT, prior to anesthesia, during the examination, and in the PACU.

Sleep quality and duration will be assessed using the Pittsburgh Sleep Quality Index (PSQI), a 19-item questionnaire (Table 3), at T1, T2, T4, T5, and T6. A patient scoring greater than 5 on the PSQI will be classified as a poor sleeper (35).

**Table 3 tab3:** The questionnaire of Pittsburgh Sleep Quality Index.

1. During the past month, when have you usually gone to bed?				
2. During the past month, how long (in minutes) has it taken you to fall asleep each night?	≤15 min (0)	16 ~ 30 min (1)	31 ~ 60 min (2)	>60 min (3)
3. During the past month, when have you usually gotten up in the morning?				
4. During the past month, how many hours of actual sleep did you get that night? (This may be different than the number of hours you spend in bed)	>7 h (0)	6 ~ 7 h (1)	5 ~ 6 h (2)	<5 h (3)
5. During the past month, how often have you had trouble sleeping because you…	Not during the past month (0)	Less than once a week (1)	Once or twice a week (2)	Three or more times a week (3)
a. Cannot get to sleep within 30 min	(0)	(1)	(2)	(3)
b. Wake up in the middle of the night or early morning	(0)	(1)	(2)	(3)
c. Have to get up to use the bathroom	(0)	(1)	(2)	(3)
d. Cannot breathe comfortably	(0)	(1)	(2)	(3)
e. Cough or snore loudly	(0)	(1)	(2)	(3)
f. Feel too cold	(0)	(1)	(2)	(3)
g. Feel too hot	(0)	(1)	(2)	(3)
h. Have bad dreams	(0)	(1)	(2)	(3)
i. Have pain	(0)	(1)	(2)	(3)
j. Other reason(s), please describe, including how often you have had trouble sleeping because of this reason(s)	(0)	(1)	(2)	(3)
6. During the past month, how often have you taken medicine (prescribed or “over the counter”) to help you sleep?	Not during the past month (0)	Less than once a week (1)	Once or twice a week (2)	Three or more times a week (3)
7. During the past month, how often have you had trouble staying awake while driving, eating meals, or engaging in social activity?	Not during the past month (0)	Less than once a week (1)	Once or twice a week (2)	Three or more times a week (3)
8. During the past month, how much of a problem has it been for you to keep up enthusiasm to get things done?	Not during the past month (0)	Less than once a week (1)	Once or twice a week (2)	Three or more times a week (3)
9. During the past month, how would you rate your sleep quality overall?	Very good (0)	Fairly good (1)	Fairly bad (2)	Very bad (3)

Component		Componen*t* score
Sleep quality	#9 Score	
Time to fall asleep	#2 Score + #5a Score (0 = 0; 1 ~ 2 = 1; 3 ~ 4 = 2; 5 ~ 6 = 3)	
Bed time	#4 Score	
Sleep efficiency	#4/(#3 – #1) * 100% (>85% = 0, 75–84% = 1, 65–74% = 2, <65% = 3)	
Somnipathy	# sum of scores 5b to 5j (0 = 0; 1 ~ 9 = 1; 10 ~ 18 = 2; 19 ~ 27 = 3)	
Hypnotics	#6 Score	
Daytime dysfunction	#7 score + #8 score (0 = 0; 1 ~ 2 = 1; 3 ~ 4 = 2; 5 ~ 6 = 3)	

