To the best of our knowledge, this study represents the first attempt to assess the effect of IMT in reducing the incidence of hypoxemia during painless gastroscopy in obese individuals. For medical ethics and safety, this randomized controlled trial (RCT) will include 232 obese patients with a BMI ranging from 35 to 39.9 kg·m^−2^, all of whom are scheduled to undergo a 4-week IMT program prior to painless gastroscopy. Additionally, we aim to compare the impact of different IMT protocols on the requirement for airway maneuvers, blood pressure, sleep quality, pro-inflammatory cytokine levels, and any potential adverse events that may arise.

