**Figure 1 fig1:**
[figure not shown]
Flow chart of the study. BMI, body mass index; ASA, American Society of Anesthesiologists; COVID-19, the coronavirus disease.

To begin, participants will undergo IMT for 4 weeks before the gastroscopy procedure. In the intervention group, IMT will be administered with a load of 30% of the Pi(max) during the first week. Starting from the second week, the load will be increased by 10% each subsequent week. Conversely, the control group will not receive any load during the 4-week IMT period.

Subsequently, all patients will receive the same sedation strategy comprising remimazolam tosilate and esketamine. The gastroscopy procedure will be performed under a stable level of sedation. After the examination, patients will be transferred to the post-anesthesia care unit (PACU) and discharged once their modified Aldrete score reaches 9.

Lastly, all data will be collected as per the schedule outlined in Table 1.

**Table 1 tab1:** The schedule of enrollment, interventions, and assessments.

Study period	Screening	Allocation	IMT		Anesthesia and examination		PACU	Follow-up		
		T1		T2		T3		T4	T5	T6

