### Data collection, handling, and monitoring

We will gather the following data for this study:

Demographic data, including age, gender, and ASA physical status classifications.Physical examination data, including HR, mean arterial pressure (MAP), SpO_2_, respiratory rate, end-tidal carbon dioxide levels, Pi(max), BMI, neck circumference, and waist-hip ratio.Data related to the primary and secondary outcomes as mentioned earlier.Requirement for vasoactive agents, such as atropine, esmolol, phenylephrine, and urapidil hydrochloride.Need for rescue sedatives.

In order to prevent any loss of follow-up, a research assistant who knows the group assignment will reach out to patients from time to time. Their purpose is to remind patients to fill out the PSQI sheets.

To ensure data integrity and security, an independent monitor will oversee the data collection process. Data collectors will enter all raw data into Excel spreadsheets, which will then be stored in a separate database with restricted access using passwords. Additionally, original data and images will be securely stored on the research center’s computer, accessible only with login passwords. Unauthorized access to the database or computer will be strictly prohibited without the monitor’s permission.

In case of any adverse events, immediate attention will be given, followed by detailed recording and continuous follow-up. The Ethics Committee will periodically review the project’s progress and decide whether it should be continued.

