### Blinding

The independent research assistant will have the responsibility of explaining the procedure and details of IMT and measuring the Pi(max) for all participants. The research assistant will conduct remote instruction and real-time monitoring of the participants through video software, making them unblinded to the process. However, both the participants and the research assistant will be explicitly instructed not to disclose any details to other researchers involved in the study.

On the other hand, the anesthesiologist, the endoscopist, data collectors, laboratory technicians, and biostatistician will be blinded to the intervention protocols and group allocation to ensure unbiased evaluation.

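### Adverse events are scheduled only for the procedure and PACU, so the 4-week training period, where the arms differ, has no scheduled or defined assessment

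*Protocol article*

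**What the plan says.** Four places in the protocol article bear on adverse events.

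- **Introduction, last paragraph (aims).** The trial is to compare the IMT protocols on several outcomes, including "any potential adverse events that may arise". No period is given.
- **Secondary outcomes.** The outcome is "monitoring of adverse events such as bradycardia, tachycardia, nausea, and vomiting". The list is open and no timing is given.
- **Table 1, outcome assessment.** The row "6) Adverse events" is marked under anesthesia/examination and under PACU, and nowhere else.
- **Data collection, handling, and monitoring.** "In case of any adverse events, immediate attention will be given, followed by detailed recording and continuous follow-up". Again no period is given.

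On treatment, the Study design section says that "participants will undergo IMT for 4 weeks before the gastroscopy procedure", with load in one arm and none in the other, and that afterwards "all patients will receive the same sedation strategy comprising remimazolam tosilate and esketamine". Under Blinding, "The research assistant will conduct remote instruction and real-time monitoring of the participants through video software", and that assistant is described as unblinded.

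**The concern.** The randomised contrast is training load over 4 weeks. An adverse effect of loaded breathing would be expected to appear first while patients are training. The schedule starts to look for adverse events only once training is over and the patient is on the endoscopy table.

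At stake is what the trial can say about the safety of IMT in this population. If the schedule is followed as printed, the by-arm comparison will rest on procedure-phase and recovery-phase events, plus whatever happens to be reported spontaneously during training. A statement that loaded IMT was well tolerated over the 4 weeks would then lack systematic data from this trial. Events during training cannot be recovered reliably long afterwards, so the gap has to be closed before training starts.

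**Working it through.** The plan gives no figure on this point, so the check is a reading of the schedule against the text.

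**1. Is the reading of Table 1 reliable?** The table came through as text, so the column positions need confirming. The columns in order are Screening, T1 (allocation), IMT, T2, anesthesia/examination, T3, PACU, T4, T5, T6. Splitting the rows by position gives:

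| Row | Columns marked | Agrees with the text? |
|---|---|---|
| Blood pressure | T1, T2, examination, PACU | Yes (Secondary outcomes) |
| Sleep quality | T1, T2, T4, T5, T6 | Yes (Secondary outcomes) |
| Cytokines | T1, T2, T3 | Yes (text after Table 3) |
| Adverse events | examination, PACU | No timing in the text to compare |

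Three rows whose timing is also given in prose come out correctly, so the adverse-event row can be trusted: 2 of 10 columns are marked, and IMT, T2 and T4 to T6 are blank.

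**2. How much randomised exposure is unscheduled?**
- Days: 4 weeks × 7 = 28.
- Breaths, from the Intervention section: 30 × 2 per day × 28 = 1,680 per patient.
- Scheduled adverse-event assessments in that period: 0, for each of the 232 patients.

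**3. Which events are named?** Bradycardia, tachycardia, nausea and vomiting. They are examples only, but all four are typical of sedation and recovery and none is specific to breathing against a load.

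**4. Does anything else fill the gap?**
- The general sentence, "In case of any adverse events, immediate attention will be given", applies once an event has come to light. It does not say that anyone asks, when, or in what words.
- The video contact is described as serving instruction, compliance and monitoring. Nothing says that it collects adverse events. Participants and the assistant are also told not to disclose details to other researchers. That is probably meant to protect the allocation, but no route from a symptom seen on video to the data record is described.
- Vital signs and blood pressure at T1 and T2 bracket the training, but they are point measurements and not a query about events in between.

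**5. Who would ask?** The assistant on video is unblinded, and the assistant who sends PSQI reminders also knows the assignment. If training events surface only through these contacts, the chance of being noted may differ by arm.

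**6. Effect on other parts of the plan.** None. The primary outcome, the 105 per group and the target of 232 do not depend on when adverse events are collected.

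**The case against.** The strongest reply is that safety during training is covered. The general sentence under data collection has no time limit and promises recording as well as a response. Participants are watched by video, vital signs are taken on both sides of the training, and the Ethics Committee reviews progress periodically. This stands to the extent that one cannot say the training period has no safety collection at all. It does not supply a scheduled or defined assessment, and the published schedule leaves that cell empty.

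A second reply is that procedure-phase events are a proper outcome. This stands in full. A reader might infer that comparing events under a common sedation regimen is uninformative because treatment is then identical. The arms still differ in prior training, and the primary outcome is measured in the same window for the same reason. The fault is that this window is the only one scheduled.

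A third reply is that an article condenses a fuller protocol, which may have a safety section. That disposes of another tempting inference, that patients who stop training would leave no recorded reason. The article is merely silent on this, and silence on such fields is not a defect. The adverse-event schedule is different: it is printed, and it does not fit the stated aim. Likewise, the description of IMT as well tolerated under Strengths is background with a citation, not a planned conclusion.

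Finally, this is a secondary outcome for a non-drug breathing exercise, and the documents give no rate of training events. The number of events that would be missed therefore cannot be estimated.

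**Conclusion.** The point holds in this form: the 4-week IMT period has no scheduled or defined adverse-event assessment, and only a general, reactive statement could cover it. That does not fit the aim of comparing the IMT protocols on any adverse events. The size is 0 scheduled assessments over about 28 days of randomised exposure per patient. No bias in the primary result and no loss of power follow from it.

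The conclusion rests on Table 1 being the operative schedule and on the column reading confirmed above. It is a matter that should be put right before training starts, since the change is small and the data are hard to reconstruct later.

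**What to change.** 1. In Table 1, mark adverse events in the IMT column. The minimum is a retrospective query at T2, when patients already complete the PSQI. T2 alone reaches only those who come to gastroscopy. The plan allows for 232 − 2 × 105 = 22 dropouts, without saying when they would occur, so collection during training is better.
2. Use one fixed question with the same wording and timing in both arms. Prefer a self-completed item, or blinded staff asking at T2, because the video and reminder contacts are run by assistants who know the allocation. Make clear that the instruction not to disclose details does not cover reporting symptoms.
3. Reconcile the aim in the Introduction, Secondary outcomes, Table 1, and the general sentence under data collection, so that all four state the same period.
4. Report training-phase and procedure-phase events separately by arm.

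Cost: some added data entry, with no new visit and no change to sample size or primary analysis. If the unblinded assistant has to ask the question, ascertainment may differ by arm, and the report should say so.
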